# Effect of breastfeeding education and support intervention (BFESI) versus routine care on timely initiation and exclusive breastfeeding in Southwest Ethiopia: study protocol for a cluster randomized controlled trial

**DOI:** 10.1186/s12887-018-1278-5

**Published:** 2018-09-26

**Keywords:** Exclusive breastfeeding, Peer education, Community-based intervention, Peer support, Early initiation of breastfeeding

## Abstract

**Background:**

Infant mortality rates are still high in Ethiopia. Breastfeeding is regarded as the simplest and least expensive strategy for reduction of infant mortality rates. Community-based educational and support interventions provided prenatally and postnatally are effective in increasing breastfeeding rates. However, such interventions are not widely implemented in Ethiopia. This study aims to assess the effect of breastfeeding education and support on timely initiation and duration of exclusive breastfeeding.

**Methods:**

A cluster-randomized controlled trial at the community level will be conducted to compare the effect of breastfeeding education and support versus routine care. The intervention will be provided by Women Development Army leaders who are already in the country’s health system using a 40-h WHO breastfeeding counseling course, “Infant and Young Child Feeding Counseling: an integrated course” and the “Training of Trainers Manual for Counseling on Maternal, Infant and Young Child Nutrition” in the local language. Culturally appropriate operational packages of information will be developed for them. Using preset criteria at least 432 pregnant women in their third trimester will be recruited from 36 zones. Visits in the intervention arm include two prenatal visits and 8 postnatal visits. Supervisory visits will be conducted monthly to each intervention zone. Data will be entered into Epi-data version 3.1 and analyzed using STATA version 13.0. All analysis will be done by intention to treat analysis. We will fit mixed-effects linear regression models for the continuous outcomes and mixed-effects linear probability models for the binary outcomes with study zone as random intercept to estimate study arm difference (intervention vs. routine education) adjusted for baseline value of the outcome and additional relevant covariates. The protocol was developed in collaboration with the Jimma Zone and Mana district Health office. Ethical clearance was obtained from the Institutional Review Board of University of Oslo and Jimma University. This study is partly funded by NORAD’s NORHED programme.

**Discussion:**

We expect that the trial will generate findings that can inform breastfeeding policies and practices in Ethiopia.

**Trial registration:**

ClinicalTrials.gov
NCT 03030651 January 25, 2017 version 3 dated 16 July 2018.

**Electronic supplementary material:**

The online version of this article (10.1186/s12887-018-1278-5) contains supplementary material, which is available to authorized users.

## Background

Breastfeeding is a unique way of providing ideal food for the healthy growth and development of infants [1]. Breastfeeding is known to have a beneficial effects in enhancing infants’ immunity, protecting against gastrointestinal and respiratory infections, reducing maternal hemorrhage, as well as the risk of breast and ovarian cancer [2–6]. Breastfeeding is associated with reduced risk of chronic diseases such as diabetes mellitus type 2 [7] and obesity [8–12].

Despite the above benefits to breastfeeding, its prevalence and duration in many countries is below the international recommendation of exclusive breastfeeding (EBF) for the first six months of life. For instance, the proportion of infants less than six months who are exclusively breastfed are 36% globally, 39% in developing countries and 31% in Sub Saharan Africa [13]. A recent systematic review has revealed that risk of all-cause and infection-related mortality was higher in predominantly, partially and non-breastfed infants compared to exclusively breastfed infants aged 0–5 months [14]. Another aspect is timely initiation of breastfeeding within one hour after delivery [15]; early initiation of breastfeeding averages about 43% globally [16]. According to the 2016 Ethiopian Demographic and Health Survey (EDHS) report, only 73% of mothers initiated timely breastfeeding and 58% of children less than 6 months old were exclusively breastfed [17].Moreover, in addition to breast milk, 17% of infants 0–5 months consumed plain water, 5% each consumed non-milk liquids or other milk whereas 11% consumed complementary foods – practices contrary to WHO’s recommendation of EBF. Additionally, 5% of infants under age 6 months are not breastfed at all. The percentage of EBF decrease sharply with age from 74% of infants age 0–1 month to 64% of age 2–3 months and, further, to 36% of infants age 4–5 months [17].

Interventions for breastfeeding promotion have been implemented using different strategies in various settings. At the policy level the extent of conferences, conventions and declarations demonstrate the global efforts in promoting breastfeeding. At the health facility level one of the strategies is the Baby Friendly Hospital Initiative (BFHI). This is a global strategy that promotes breastfeeding in maternity wards around the time of delivery based on the ten steps to successful breastfeeding model [18]; Studies have established the effectiveness of the BFHI-approach in promoting optimal breastfeeding practices particularly in developed countries where the majority of women deliver in health facilities [19–22]. Nevertheless, the effectiveness of the BFHI as well as training of health workers might be limited in developing countries where the majority of deliveries occur at home.

Community- based interventions have been employed in different parts of the world during pregnancy and/or the postnatal period on an individual or group basis, through health facilities or home visiting programmes, using professional education/counselling and peer counselling/support. Most studies on the effectiveness of using peer support/counsellors have reported increased levels of early initiation of breastfeeding and EBF [20, 23–27].

A systematic review of 52 studies from 21 countries revealed that all forms of extra support including lay and professional, analyzed together showed an increase in duration of ‘any breastfeeding’ as well as the duration of EBF. However, the most effective support is provided in person and on a recurring basis at regular scheduled visits [28]. Among breastfeeding promotion interventions involving peer counsellors for support of EBF few studies are from sub-Saharan Africa [29–31].

In Ethiopia, a few behavior change interventions aimed at improving the Infant and Young Child Feeding practice have been conducted by the Non-governmental organizations (NGOs) projects [32–34]. The reports of these projects focus either on implementation fidelity [33], or are implementation research [32] and large scale in scope, focusing not only on breastfeeding but also on other Infant and Young Child Feeding practices [34]. Moreover, none of the interventions were provided during pregnancy as well as the postnatal period and none of the projects used control groups except a trial conducted in Hawassa city [35]. In that trial, the intervention consisted of only one prenatal educational session [35].

The aim of the planned trial is to examine the effect of breastfeeding education and support intervention on timely initiation and duration of EBF in a cluster randomized community based behavioral promotion trial.

### Study objectives/hypotheses

**Research Hypothesis** – Breastfeeding education and support intervention is superior to usual care in improving timely initiation of breastfeeding, exclusive breastfeeding and growth.

**Primary objective -** To determine if breastfeeding education and support intervention is superior to usual care in improving timely initiation of breastfeeding, exclusive breastfeeding and growth.

**Secondary objectives –** the main secondary objectives areTo validate the Afan Oromo version breastfeeding knowledge and attitude questionnaire.To assess baseline knowledge, attitude and practice of mothers on breastfeeding.To examine the effect of breastfeeding education and support intervention on mothers’ knowledge and attitude towards breastfeeding.To assess the experiences of breastfeeding mothers and WDA leaders participating in the breastfeeding education and support intervention.

## Methods/design

### Design

A cluster randomized controlled single-blind parallel-group, two-arm, superiority trial with 1:1 allocation ratio was designed to investigate whether a breastfeeding education and support intervention provided prenatally and postnatal period increase timely initiation, exclusive breastfeeding duration and infant growth among women in Mana district, Jimma zone, Southwest Ethiopia. This study design was chosen in order to avoid contamination among treatment groups. Clusters are zones found in Mana district, Jimma (Fig. 1).

**Fig. 1 Fig1:**
[figure not shown]
Flow of participants

### Setting

The study will be conducted in the Jimma Zone which is one of 17 administrative zones of the Oromia region, Southwest Ethiopia. Its capital Jimma is situated 352 km to the Southwest of Addis Ababa. Jimma Zone has 17 districts and one special zone. According to population projection of Ethiopia for all Regions at district level from 2014 to 2017, which is based on the 2007 national census, the zone has a total population of 3.1 million in 2016. The rural part accounts for 80.2% of the total population; Oromo is the dominant ethnic group in the area. Health services are provided through 3 hospitals, 112 health centers and 498 health posts. In the Oromia Region a total of 147,428 Health Development Army (HDA) groups and 732,259 one-to-five networks were established in 2011 [36]. The one-to-five networks are women volunteers who are empowered as a HDA to transform their society. They are trained to focus more intensively on sparking local behavior change making regular rounds to check on neighbors and encourage practices like latrine building and setting-up separate cooking spaces. They are from “model families” and serve as living examples that the health extension workers’ messages are being heard [37]. The proportion of women of child bearing age is 24% [38]. The trial will be conducted in the Mana district which is one of the 17 districts found in the Jimma zone. The district has 26 kebeles - the lowest administrative unit and each kebele is divided into three small zones (Fig. 2).

**Fig. 2 Fig2:**
[figure not shown]
Flow diagram of structures in the Oromia region and the jimma zone

### The context

#### Health extension program

As part of an accelerated primary health care expansion to the community the government of Ethiopia launched its health extension program (HEP), an innovative community-based strategy to deliver preventive and promotive services, and selected high impact curative interventions at community level in 2003. In addition to the construction of health posts and provision of supplies, the implementation strategy of HEP focused on building human resource by deploying two salaried female Health Extension Workers (HEWs) at health posts in each kebele (village) of the country [39]. All HEW trainees are women aged 18 and above with a minimum of 10th grade schooling. In order to increase acceptance, these HEWs are drawn from the communities in which they serve. They complete a one year training of courses and field work that is provided by Technical and Vocational Education Training Schools (TVETs), operated by the Ministry of Education. Upon completion, two HEWs are assigned to each health post which serves as the basis for the HEP [40].

HEWs promote the 16 health packages in the HEP consisting of disease prevention and control, family health, hygiene and environmental sanitation as well as health education and communication [40]. HEWs implement the health promotion program through house to house visits. The interventions include: promotion and provision of contraceptives, antenatal care including nutritional advice and micronutrient supplementation, clean delivery, basic new-born care, child nutrition (such as exclusive breastfeeding, complementary feeding, cooking nutritious meals, and vitamin A supplementation), immunization, use of mosquito bed nets, HIV prevention, sanitation, and hygiene (including support and supervision in the construction of latrines, disposal pits and healthful homes) [41]. HEWs spend 75% of their time visiting families in their homes implementing promotional and preventive interventions to create appropriate healthy behaviors and to improve knowledge and attitude toward health-seeking behaviors.

The remaining 25% of their time is spent providing the following services at the health post: immunization, health education, antenatal care, family planning; delivery and postnatal care, growth monitoring of children, community treatment of severe acute malnutrition, diagnosis and treatment of malaria, diagnosis and treatment of pneumonia, treatment of diarrhoea with oral rehydration fluids, treatment of eye infections with eye ointment, treatment of selected skin problems with ointments, Vitamin A supplementation, first aid, referral of difficult cases, documentation, and reporting. The HEWs’ community outreach activities include promoting model families, community groups or households [41, 42]. At least two diploma level midwives and one health officer with emergency obstetric care training support HEWs from the local health center [43].

The HEW selects “model families” in collaboration with the village administration. Model families are households who receive 96 h of training and adopt all 16 HEP packages [41] – from vaccinating their children and sleeping under mosquito bed-nets to building separate latrines and using family planning [42]. The training involves face-to-face teaching and household visits in four modules corresponding to the four HEP subprograms: prevention of communicable diseases, family health, environmental and household sanitation, and health education. Model families are expected to disseminate their knowledge and behavior to other households in order to support the HEWs’ efforts [44].

#### Antenatal and postnatal care

Within their catchment area, HEWs are responsible for identifying pregnant women, providing antenatal care (ANC) and connecting them with the formal health system in the event of elevated risk or complications. They provide four focused ANC visits throughout a woman’s pregnancy using an integrated maternal and child care card. Women see the same HEW for all four home visits: first visit after 16 weeks of pregnancy, second visit between weeks 24–28, third visit between weeks 30–32 and fourth visit between weeks 36–40. The HEW conducts a general physical examination and evaluation at each visit, checking the mother and the growth of the foetus. HEWs also assess all pregnancies for the potential risks by communicating with women and their families about the danger signs of complications so that there is a shared responsibility for identification and action when needed. Furthermore, HEWs develop an individualized birth preparedness and complication readiness plan with each woman, involving the women’s partner or support whenever possible [43].

During delivery, the same HEW is able to assist by accompanying a woman to a health facility for delivery. HEWs are trained in pre-referral clinical procedures such as starting intravenous fluids and catheterization [45]. After delivery, HEWs do follow up visits during the postnatal period when care is critical for both mother and new-born. The initial postnatal care visit occurs ideally within four hours of delivery [46]. They conduct the next follow-up postnatal visits at two days, six days, and six weeks [43].

#### Women development Army (WDA) groups

In 2011 the government started the Health Development Army (HDA) with the aim to consolidate the gains made as a result of roll out of the HEP and promote community ownership of the programs. The program was first tested in Tigray and then introduced to the four big regions of the country. Although some regions have both male and female HDAs, HDAs are now basically women known as the women development army (WDA) [38].

WDAs are identified from the model families. As soon as the WDA groups are formed through a participatory community engagement, the WDA leaders go through an intensive 7 to 10 days training program [38], whose primary task is to educate and mobilize communities to use available high impact maternal, neonatal and child health (MNCH) services provided by the health post and health centres [42]. In a kebele of 1000 households, averages of 150 leaders go through the training program that is supported by the local PHC unit and the woreda (district) health office. In an average kebele, there are approximately 30 WDA team leaders and 200 WDA network leaders [38].

Each WDA group consists of 25–30 households (women) which are further organized into the “1 to 5” network of women where a model woman leads five other women within her neighbourhood [47]. Designed to empower women in particular and the family in general in health decision making leading to democratization of health and to community partnership, the one-to-five network functions as a forum for exchange of concerns, priorities, problems and decisions related to the health status of women. While being supported by the HEWs the networks are responsible for the preparation of plans and ensuring their completion, for the collection of health information, and also for conducting weekly meeting to review progress and submitting monthly reports [41]. The WDA groups thus support the implementation of the HEP (Fig. 3).

**Fig. 3 Fig3:**
[figure not shown]
Hierarchy of reporting

The one-to-five networks meet every week, while the larger health development team meets once every two weeks. Furthermore, they review their performance against their plan and evaluate each other on monthly basis and give grades A, B, and C for top, middle and poor performers, respectively. A performance report including the grades is organized at the health development team level and sent to the HEWs [38].

#### Eligibility criteria for clusters and WDA leaders

Out of 78 zones found in Mana district, 36 clusters that are not adjacent to each other and have geographical accessibility will be selected randomly for the study - 18 intervention and 18 controls.

Women development army leaders, one from each selected zone, who are influential members of their community will be selected by maternal health focal person at Mana district health office.

#### Eligibility criteria for participants

Participants for this trial will be healthy pregnant women in their third trimester. We will recruit them using a 2-stage screening process. An initial screening will take place while women are pregnant; the second screening will take place after delivery to ascertain whether both mother and infant are qualified for inclusion. Inclusion criteria during pregnancy will be pregnant women in the third trimester, living in the selected cluster with no plans to move away during the intervention period, without psychiatric illness, capable of giving informed consent and willing to be visited by supervisors and data collectors. Inclusion criteria after delivery will be a singleton live birth with no severe malformation that could interfere with breastfeeding. Exclusion criteria will be maternal death, women with severe psychological illness which could interfere with consent and study participation, severely ill or clinical complications warranting hospitalization, stillbirth, infant death, twin gestation, or preterm birth (at < 37 weeks gestation).

#### Sample size determination

Sample size was calculated using Sample Size Calculator (SSC) a Windows based software package [48] with the following assumptions: to detect an increase in exclusive breastfeeding for 6 months from 58 to 78% [17], with 95% CIs and 80% power, assuming an intra-cluster correlation coefficient of 0·1 equal to the Ugandan study [49] for a cluster size of 10, it was calculated that we will need 36 clusters. Adding 20% of the sample size for loss to follow-up, the final sample size is 432 pregnant women (216 in intervention, and 216 in control groups).

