## Discussion

At the beginning, the aim was to include all pregnant women in selected clusters who are in their third trimester. However, when recruitment was started, we failed to get intended number of women in each cluster. As one of the purposes of using cluster randomized controlled trial is to prevent information contamination among study participants, we could not increase number of clusters beyond 36 and also there was a logistic constraint to expand the trial into another district. Therefore, we included women who are in their second trimester to fill our sample size; however, the intervention for these women will start when they are in their third trimester. This will inevitably prolong the intervention duration for a few months. If this intervention proves to be effective in improving the timely initiation and exclusive breastfeeding rates, it will be scaled up in other parts of Oromia region and other regions of the country.

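### The sample size uses a pooled 0–5 month prevalence (58%) as the control rate for exclusive breastfeeding at six months, so the stated 80% power was calculated for a different quantity

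*Protocol article*

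**What the plan says.** Under Sample size determination, the protocol article plans "to detect an increase in exclusive breastfeeding for 6 months from 58 to 78" per cent, with reference [17] as the source. It assumes 80% power, 95% confidence, an intra-cluster correlation of 0.1 and 10 women per cluster, and arrives at 36 clusters. It continues: "Adding 20% of the sample size for loss to follow-up, the final sample size is 432 pregnant women".

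The Background takes its figures from the same reference: "58% of children less than 6 months old were exclusively breastfed [17]". It then says that the proportion falls sharply with age, from 74% at 0–1 month to 64% at 2–3 months and "to 36% of infants age 4–5 months [17]".

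Outcome assessment defines the primary breastfeeding outcome as the proportion giving only breast milk at six months. Data processing and analysis says that effects on binary outcomes will be reported as risk differences in percentage points.

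**The concern.** The 58% in the sample size paragraph is labelled as a six-month rate. In the Background, the same figure from the same reference is the prevalence over all ages from birth to under six months. The simple mean of the three age-band figures, (74 + 64 + 36)/3, is exactly 58. The protocol gives no other reason for expecting 58% of controls to be exclusively breastfeeding at six months, and its own nearest-age figure is 22 points lower.

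This is the only power statement in the article. Readers will judge a null or small effect on exclusive breastfeeding against it, although the 80% was not worked out for that outcome. The 20-point target was also never set against a rate for the right age.

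**Working it through.** **Inputs from the protocol article.** Control 58% and target 78%, power 80%, ICC 0.1, 10 per cluster, 36 clusters, 20% added for loss (Sample size determination). Two-sided 5% level (Data processing and analysis). 36% at 4–5 months (Background). Design effect: 1 + (10 − 1) × 0.1 = 1.9.

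**Reproducing the stated figure.** Two-proportion formula per arm, with p̄ = (p1 + p2)/2 and d = p2 − p1:

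n = [1.96·√(2p̄(1 − p̄)) + 0.84·√(p1(1 − p1) + p2(1 − p2))]² / d²

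With continuity correction: n′ = (n/4)·[1 + √(1 + 4/(n·d))]²

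- 58% vs 78%: n = 84.2 and n′ = 93.9. Then 93.9 × 1.9 = 178.5 per arm, which is 18 clusters of 10 per arm, or 36 in all. This matches.
- 360 × 1.2 = 432. This matches.

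So 58% did drive the design. The fault lies in an input, not in the calculation.

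**Same formula at the nearest-age rate, keeping 20 points.**

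- 36% vs 56%: n = 96.3 and n′ = 106.1. Then 106.1 × 1.9 = 201.5, about 202 women per arm against 180 planned. In whole clusters of 10 that is 21 per arm, or 42 in all.
- Solving the continuity-corrected formula for power at 180/1.9 = 94.7 effective women per arm gives 80.4% for 58% vs 78% and 74.8% for 36% vs 56%.

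**Power by noncentral t.** This uses 34 df (36 zones − 2) and no continuity correction. SE = √([p1(1 − p1) + p2(1 − p2)] × 1.9/180), and the noncentrality is d/SE. Example for 36% vs 56%: SE = √(0.4768 × 1.9/180) = 0.0709, and 0.20/0.0709 = 2.82.

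| Control → intervention | Basis | Power |
|---|---|---|
| 58 → 78% | as planned | 83.5% |
| 36 → 56% | 20 points | 78.2% |
| 30 → 50% | 20 points | 79.6% |
| 25 → 45% | 20 points | 81.8% |
| 20 → 40% | 20 points | 84.8% |
| 36 → 48% | constant rate ratio (78/58) | 37–39% |
| 36 → 59% | constant odds ratio (2.57) | 89% |

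The rate-ratio row is a range because 36 × 78/58 = 48.4% gives 39% and a rounded 48% gives 37%. The control rates below 36% and the two ratio transfers are assumptions; no section of the protocol states them.

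The two methods should not be mixed. Like for like, the change from 58% to 36% with a 20-point gain is 80.4% to 74.8% by the continuity-corrected formula, and 83.5% to 78.2% by noncentral t.

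**Loss allowance.** 432 × 0.8 = 346, which is below the 360 the calculation requires. Covering 20% loss needs 360/0.8 = 450. The loss that 432 does cover is 1 − 360/432 = 16.7%. With 9.6 women per zone instead of 10, noncentral t power falls from 83.5% to 82.8% (58 → 78%) and from 78.2% to 77.4% (36 → 56%), under one point in each case.

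**The case against.** The strongest reply is that power hardly moves on the scale the trial plans to use. The target is an absolute 20 points and the analysis reports risk differences. On that scale, noncentral t power is about 78% at a 36% control rate and passes 80% again by 25%. That stands, and it is why the point is not graver.

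A reader might infer that the trial is badly underpowered because a constant rate ratio gives only 37–39%. The documents do not support this as the expected case: no section plans a relative gain, and a constant odds ratio from the same starting point gives about 89%.

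A reader might also infer that the control rate must be 36% or less. The reported decline with age makes a lower rate plausible. But 36% is a national survey figure for 4–5 months, and the documents give no rate for exactly six months or for the study district, which was chosen purposively. It has to be treated as an assumption.

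Finally, the Discussion says that "when recruitment was started, we failed to get intended number of women in each cluster", which might suggest uneven zones and a further loss of power. The same section says that second-trimester women were then included to make up the number, and Trial status reports recruitment complete. Final zone sizes are not given, so no loss from unequal clusters can be quantified.

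On the loss allowance, adding 20% to 360 does give 432, so the sentence is literally correct. It does not deliver the protection against 20% loss that it is there to provide.

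None of this supports 58% as a six-month rate.

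**Conclusion.** The point holds as a wrong input to the only power statement. The 58% is an age-pooled prevalence, the outcome is at six months, and the nearest-age figure from the same reference is 36%. With a 20-point gain from 36%, 36 zones of 10 and ICC 0.1, power is about 75% by the protocol's apparent formula and about 78% by noncentral t. That is a shortfall of some 2 to 5 points against the stated 80%. Whether power is lower or higher than stated depends on the true control rate and on how the effect carries over, neither of which the documents settle. What can be said firmly is that 80% has not been established for this outcome and that the 20-point target has not been justified against a suitable rate. The loss-allowance slip is real but minor. This should be fixed; it is not a fatal flaw.

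**What to change.** Rewrite the sample size paragraph as follows.

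- State the control rate for exclusive breastfeeding at six months as an assumption with a range, 36% and lower, and say that no district rate or exact six-month rate was available. Describe 58% as what it is, or remove it.
- Justify the target difference against that rate.
- Report the power of the fixed 36 zones with about 346 analysed women, over a range of control rates and of differences that includes some below 20 points. Name the method, including whether a continuity correction is used.
- Say that 432 women cover 16.7% loss, or that about 346 remain if 20% are lost.

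No extra enrolment, design change or analysis change is needed. Trial status says six-month data collection has only begun, so the correction can still be made before those outcome data are complete. The cost is one paragraph, and the stated power may turn out somewhat less favourable.
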